## Abstract

**Background:** Enhancing patient participation is becoming increasingly important in mental health care as patients use to have a dependent, inactive role and nonadherence to treatment is a regular problem. Research shows promising results of initiatives stimulating patient participation in partnership with their clinicians. However, few initiatives targeting both patients' and clinicians' behaviour have been evaluated in randomised trials (RCT). Therefore, in GGz Breburg, a specialized mental health institution, a digital intake approach was developed aimed at exploring treatment needs, expectations and preferences of patients intended to prepare patients for the intake consultations. Subsequently, patients and clinicians discuss this information during intake consultations and make shared decisions about options in treatment. The aim of this trial is to test the efficacy of this new digital intake approach facilitated by Routine Outcome Monitoring (ROM), peer support and training of clinicians as compared to the intake as usual. The primary outcome is decisional conflict about choices in treatment. Secondary outcomes focus on patient participation, shared decision making, working alliance, adherence to treatment and clinical outcomes.

**Methods:** This article presents the study protocol of a cluster-randomised controlled trial in four outpatient departments for adults with depression, anxiety and personality disorders, working in two different regions. Randomisation is done between two similar intake-teams within each department. In the four intervention teams the new intake approach is implemented. The four control teams apply the intake as usual and will implement the new approach after the completion of the study. In total 176 patients are projected to participate in the study. Data collection will be at baseline, and at two weeks and two months after the intake.

**Discussion:** This study will potentially demonstrate the efficacy of the new digital intake approach in mental health care in terms of the primary outcome the degree of decisional conflict about choices in treatment. The findings of this study may contribute to the roll out of such eHealth initiatives fostering patient involvement in decision making about their treatment.

**Trial registration:** Trial registration: Dutch Trial Register NTR5677. Registered 17th January 2016.

## Background

The enhancement of patient participation in health care is deemed to be of great importance [1–3]. Research has pointed out that patients who take an active role in their treatment are often more satisfied and feel more in control with the health care they receive, are more able to manage their own mental health, have better treatment adherence, report a higher quality of life, and show better health outcomes [4–10].

Despite the importance of patient participation, the literature offers no univocal definition of this concept [10, 11]. In this study we choose the most commonly used definition of patient participation, referring to patient involvement in decision making about their health care [10, 12]. This way, patient participation, which includes behaviours such as providing information, asking questions and preparing for consultations, is an issue closely related to Shared Decision Making (SDM) [13]. SDM is defined as a collaborative approach in which clinicians and patients share the best available information when making clinical decisions, and where patients are supported to consider options to achieve informed preferences [14]. In Dutch mental health care, the importance of patient participation is emphasized by a range of initiatives aimed at stimulating Shared Decision Making [15–18]. There is growing evidence of the benefits of SDM in mental health care. Research has shown that SDM in mental health care leads to better informed and more actively engaged patients, more patient satisfaction, less decisional conflict and better patient treatment adherence [19–29].

In spite of the interest and the potential of SDM approaches in mental health care, to date many patients still have a dependent, inactive role in mental health treatment, believing ‘clinicians know best’ and expecting clinicians to make decisions in treatment [15, 16, 28–31]. Fostering patient engagement and SDM in mental health care is, therefore, essential. More initiatives are needed to support the decisional capacity, participation and active behaviour of patients in treatment granting them more choice and control regarding their own mental health care, to provide a more equitable and collaborative working relationship and to enhance shared decision making [1, 4, 13, 32].

Previous studies have shown that both the attitudes of clinicians and patients influence patient participation and joint decision making [8, 13, 30, 33–35]. The power imbalance between patients and clinicians is deemed to be a key barrier in making shared decisions [36]. Few initiatives targeting both patients’ and clinicians’ behaviour have been conducted and evaluated [33]. This underlines the need for new initiatives that aim to support patients as well as to modify clinicians’ attitudes [13, 35, 36].

It should be noted, however, that not all patients are equally capable to participate in their treatment process. Adequately fulfilling this role depends on interests, skills and support that patients receive [4, 5]. Furthermore, the patient-clinician working alliance has a great influence on the degree of patient participation in decision making [37, 38]. The working alliance between patient and clinician refers to the collaborative relationship between patient and clinicians and includes communication style, the quality of the relationship, agreement on goals and tasks and mutual decision making [37–41]. The patient-clinician relationship is an important basis for sharing treatment decisions [37, 38]. Several studies have demonstrated the positive correlation between the quality of the patient-clinician alliance with treatment adherence and clinical outcomes [9, 40, 42, 43].

## Rationale

As described above, a reversal in the current practice, focused on attitudinal changes at the level of patients as well as clinicians from the start of treatment on, is needed to mobilise and facilitate patients to participate in mental health treatment. Therefore, GGz Breburg, a specialized mental health institute in the southern part of the Netherlands, will implement a digital intake approach incorporating eHealth interventions integrated with Routine Outcome Monitoring, which implies regular measurements of clinical outcomes during treatment (for details see page 7), and facilitated by consultation of peers and clinicians’ training. It aims to explore treatment needs, expectations and preferences of patients and discussing this information with the clinicians during intake consultations. This digital intake approach is expected to influence both sides of the therapeutic dyad in a positive way and will be implemented in four outpatient departments, for adults with depression, anxiety and personality disorders. Such a combined initiative in the intake process has not been tested in a randomised controlled trial.

## Aim and hypotheses

Aim of this trial is to test the efficacy of a digital exploration of patients’ treatment preferences at intake facilitated by Routine Outcome Monitoring (ROM), peer support and training of clinicians in terms of the primary outcome the degree of decisional conflict, as an important result of patient participation and shared decision making [26, 44]. This manuscript will report on the development of this new digital intake approach and the design of the study that will be conducted to evaluate this approach.

The first hypothesis is that, compared to the intake as usual, the new intake method will lead to less decisional conflict about choices in treatment. The second hypothesis is that the implementation of the new intake method

enhances patient participation, stimulates the process of shared decision making, improves the working alliance between patients and clinicians, and finally has positive effects on the adherence to treatment and clinical outcomes.

Methods/Design

Trial design

This study is designed as a two-arm matched-pair cluster-randomised controlled trial with two conditions: 1. A digital intake process with eHealth interventions integrated with two consecutive Routine Outcome Monitoring (ROM) measurements and consultation of peers supporting patients to participate from the beginning of treatment along with training and coaching of clinicians to adopt the changing roles; 2. The intake as usual with a single ROM measurement and without eHealth interventions, peer support and training of clinicians. The control teams will implement the new intake process after the completion of the data-collection.

Participants and setting

This study will be conducted in four outpatient departments of a specialised mental health institution GGz Breburg, located in the southern part of the Netherlands. Annually, more than 14.000 patients are treated by about 2000 employees at GGz Breburg. The digital intake approach will be being tested among various diagnostic groups (patients with depression, anxiety and personality disorders as their primary diagnosis). Two of the participating departments are specialised in treating patients with depression and anxiety disorders; each operating in a separate geographical catchment area. The other two departments are specialised in personality disorders and are active in separate catchment areas. The four participating departments are each divided into two teams of clinicians who perform intakes (Fig. 1). Each team of intake-clinicians have their own multidisciplinary team consultation, in which treatment policy at the patient level is discussed and checked. Due to the matched pair design at the level of intake-teams within each department, in total four intervention and four control teams participate. In accordance to the sample size calculation (see section

sample size, page 18) 176 patients will be included (88 in the intervention and 88 in the control teams), with an average of 44 patients per department (22 intervention and 22 control).

Inclusion and exclusion

Patients from the participating departments will be invited for participation in this study if a) a full intake is planned and b) when they are fluent in Dutch. Patients who meet these criteria will be asked for written informed consent. Patients will be excluded form the study if they do not receive a full intake and do not have adequate Dutch language skills (verbal and written).

Randomisation and blinding

A cluster randomised design at the level of intake-teams and participation of intake-teams in separate multidisciplinary consultations will serve to limit contamination effects between intervention and control groups [45]. The pairs of intake groups within a department are randomly assigned to either the experimental or control condition (matched pairs). The matched teams within each department perform intakes for a similar population of patients in a similar geographic catchment area and have similar personnel. Randomisation of the intake-teams is conducted by an independent researcher, using a syntax in SPSS, which allocates the matched pairs to the control (code 0) or intervention group (code 1). To reduce bias, data collection for this study will be carried out by research assistants, independent of the principal investigator and treatment, with self-report instruments completed by both patients and clinicians. This results are not visible at patient level during intake and treatment. Only the outcome parameters no-show, drop-out and clinical outcome (ROM) will be collected in the context of treatment. As is common practice in cluster randomised RCTs, propensity analyses will be performed at the analytical stage to correct for possible biases in the randomisation process [45].

During inclusion, while informing patients and asking them for written informed consent, the research assistants are blinded for the study arm. The questionnaires

[figure not shown]

Fig. 1 Participating departments and intake teams

are based on self report and hence do not require assessment by a research assistant. Due to the randomisation at the team level and the nature of the intervention, blinding of the clinicians and patients is impossible.

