### Intervention and control

The intervention teams implement an intake intervention consisting of four parts: eHealth modules, Routine Outcome Monitoring, peer support and training of clinicians.

Firstly, eHealth modules are an accessible way for patients to prepare the face to face consultations together with relatives, offer opportunities for patients to participate actively in treatment and support shared decision making [46–48]. Secondly, Routine Outcome Monitoring (ROM) is integral part of the digital intake approach. ROM implies regular measurement of clinical outcomes, at the beginning, during and at the end of treatment, aiming to provide feedback (e.g. with graphics) on the patients' progress during treatment and use the information to adjust treatment [49–52]. At the intake (and later on during treatment), ROM is a useful tool to involve patients in their treatment process by means of providing information by which shared decisions are made about treatment [18, 53]. In this initiative, ROM results visualised in a graphic environment, are presented as 'the recovery trajectory of the patient'. The participating departments all use the same ROM questionnaire which measures symptoms and functioning. Two ROM measurements in the intake process may contribute to meaningful results which are not dependent on a single measurement point. Thirdly, the availability of peers for counselling is a promising approach empowering patients to participate in treatment [54]. Finally, training of clinicians and follow-up training sessions take place to stimulate and facilitate the requested changing roles of clinicians and patients [36] in the new intake approach.

The eHealth modules are designed to explore treatment needs, expectations and preferences of patients. With these modules patients prepare themselves, along with relatives, for the face to face intake consultations, which are intended to lower decisional conflict, stimulate patient participation and facilitate the dialogue between patients and clinicians about choices in treatment. The content of the eHealth modules is described in Table 1.

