### Study flow

Patients who are referred to one of the participating departments, are invited for an intake consult. Patients

who are planned for an intake consultation with a clinician of the intervention group, are assigned to the intervention team and will get the new eHealth intake automatically. Patients who have this first appointment with a clinician of the control group, are assigned to the control group and will follow the intake as usual. In addition, both groups of patients, who follow the new intake process and the intake as usual, will be invited to participate in the evaluation research consecutively. Research assistants inform all patients (who meet the inclusion criteria) about the research, ask them to participate in the study and obtain written informed consent.

Three measurement points will be scheduled (see Table 2): baseline assessment (T0) and two measurements (T1, T2) after the intake (T1 = two weeks after intake, T2 = two months after intake). Because only T1 and T2 contains additional questionnaires for this research, written informed consent will be asked during the first face to face appointment, just before T1. Patients who give informed consent for the research, are completing self-report questionnaires organised by independent research assistants. In addition to T1, clinicians answer questions about shared decision making regarding their patients. Patients and clinicians who participate in the study, receive a request by email to complete the questionnaires. If necessary, one week later they get a reminder by email. After nine and fourteen days the research assistant calls patients who have not yet

**Table 2** Measurement points

| Assessment/Questionnaire                                                                                                                    | Baseline (T0) | 2 weeks after intake (T1) | 2 months after intake (T2) |
|---------------------------------------------------------------------------------------------------------------------------------------------|---------------|---------------------------|----------------------------|
| Primary Outcome Parameter                                                                                                            |               |                           |                            |

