  - 5) Patient-Doctor Relationship Questionnaire (PDRQ-9) [64].

The SDM-process will be measured with the Shared Decision Making-Questionnaire-9 (SDM-Q-9) [61, 62], which has Dutch versions for patients and clinicians [18, 63]. Both versions ask the patient and clinician first to enter the health problem the consultation was about and which decision was made. The questionnaire continues with nine items about the steps in the SDM process, scoring at a 6-point Likert scale that ranges from 0 (completely disagree) to 5 (completely agree). A total score can be calculated by summing the scores of all items. A high score indicates more SDM. The SDM-Q-9 shows a high reliability [61, 62]. The available results about the factorial validity are also positive [61, 62]. The psychometric testing of the Dutch version of the SDM-Q-9 [63] demonstrated good acceptance, internal consistency, and acceptable to good convergent validity of the versions for patients and physicians. Patients will be asked to complete the SDM-Q-9 at T1 and T2. At T1 clinicians will complete the same questions regarding the consultations with their patients.

The PDRQ-9 will measure the working alliance. The PDRQ-9 consists of 9 items and measures the therapeutic aspects of the clinician-patient relationship from a patient point of view. The items focus on the empathic style and availability of the clinician and are answered on a 5-point Likert scale (1 = not at all appropriate to 5 = totally appropriate). Two sample items are: 'My clinician understands me' and 'My clinician and I agree on the nature of my medical symptoms'. A mean score of all nine items is calculated. A higher score means more satisfaction about the relationship. The psychometric quality of the Dutch PDRQ-9 shows good internal consistency, adequate test-retest reliability and the ability to discriminate between patient groups [64].

Next the patients' adherence to treatment will be investigated. Adherence can be defined as the extent to which the patient's behaviour concur with the advice of the clinician [9]. In this study adherence is operationalised as the number of missed appointments (no-shows) and patients who do not want to proceed with treatment

(early treatment drop out). These data will be extracted from the electronic patient records.

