#### **Treatment integrity**

To check the treatment integrity, during the implementation and period of data collection, process indicators will be assessed. These indicators will report the degree of completion of the eHealth modules (registered by research assistants in the research database), number of completed ROM measurements (data extraction from electronic patient records) and the extent of using peer support (registered by peers themselves).

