A second strength is that the additional data collection for this research is carried out independent of the treatment. Separately for this study patients fill out questions about decisional conflict, participation in mental health treatment, shared decision making and the working alliance with the clinician. This results are not visible at patient level during intake and treatment. Data collection is conducted by independent research assistants. This approach diminishes undesired influence of the research team or clinicians on the results, reduces the chance of social desirable answers and enhances uniformity and quality of the collected data. Only the outcome parameters no-show, drop-out and clinical outcome (ROM) will be collected in the context of treatment.

The third strength of the study is that at T1, both the patients and clinicians are invited to complete a questionnaire about decisional conflict and shared decision making. If there are different views between patients and clinicians about the application of shared decision making, they will be detected and further analysed.

Finally, the study is conducted in four departments working in two regions and treating different diagnostic groups (depression, anxiety and personality disorders). Because the data collection takes place in real world clinical practice and in several departments the results will be generalizable to a broader group of mental health care teams, clinicians and patients with depression, anxiety and personality disorders.

The study brings about some limitations that could influence the results. First, the clinicians are not blinded for the design. It is possible that clinicians, working in the control teams, make additional efforts to stimulate patient participation, to improve the quality of the working alliance and to applicate shared decision making. Although, the research assistants are partially blinded for the study arm, they are less likely to influence the results, because the outcome parameters are measured

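### The protocol ties the SQ-48 to treatment yet schedules it at T1 and T2 for all patients, and states no route to a score once a patient stops treatment

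*Protocol*

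**What the plan says.** Under Randomisation and blinding, the protocol gives data collection to research assistants who are independent of treatment, then makes an exception: "Only the outcome parameters no-show, drop-out and clinical outcome (ROM) will be collected in the context of treatment". The Discussion repeats that sentence. It also lists the forms kept apart from care, the last being about the alliance with the treating professional: "Separately for this study patients fill out questions about decisional conflict, participation in mental health treatment, shared decision making and the working alliance with the" (the quotation stops one word short of the end of the sentence). The SQ-48 is not on that list.

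Table 2 treats ROM and the SQ-48 as the same instrument. It marks it with an X at T0, T1 and T2, where "T1 = two weeks after intake, T2 = two months after intake". In the same table, no-show and drop-out are marked as taken from the patient record.

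Intervention and control describes ROM by the course of care: "ROM implies regular measurement of clinical outcomes, at the beginning, during and at the end of treatment". The Treatment integrity section counts ROM from the record: "number of completed ROM measurements (data extraction from electronic patient records").

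On adherence, Secondary outcome measures states: "In this study adherence is operationalised as the number of missed appointments (no-shows) and patients who do not want to proceed with treatment". The second hypothesis is that the new intake, among other things, "finally has positive effects on the adherence to treatment and clinical outcomes".

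The research follow-up is described under Study flow: "Patients who give informed consent for the research, are completing self-report questionnaires organised by independent research assistants". It uses e-mail, a reminder, telephone calls, and paper forms for patients without internet. Nothing limits it to patients still in treatment, and nothing says that it carries the SQ-48.

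**The concern.** Two statements about one outcome do not fit together. The table promises a score at fixed times for everyone, while the text places collection of that score inside treatment. For a patient who leaves before T2, the protocol does not say who asks for the SQ-48, or how.

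This matters because leaving treatment is not a neutral event here. It happens after randomisation, it is an outcome, and the trial expects the intervention to reduce it. If scores exist mainly for patients who stay, the arms are compared on groups selected by something the intervention may change. Suppose leavers have more distress than stayers. The arm with more drop-out then loses more of its high scores and looks better than it is. An intervention that succeeded in keeping patients in care would be penalised on the symptom outcome. Scores never requested cannot be recovered at the analysis stage.

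**Working it through.** **1. Is there a stated route to a T2 score after treatment stops?**

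- Randomisation and blinding, and Discussion: the SQ-48 is grouped with no-show and drop-out as collected through treatment, in contrast to the research forms.
- Discussion: four constructs are collected separately for the study, and symptoms are not among them.
- Intervention and control: the only ROM moments with a described mechanism are at intake. Usual care has one, linked to the intake consultation. The new intake has two, one in the first eHealth module and one linked to the consultation. No ROM at two weeks or two months is described.
- Table 2: X at T1 and T2, with no mechanism given.
- Study flow: a mechanism that could reach leavers exists, but the SQ-48 is not assigned to it.

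So a T2 score is scheduled for all, but no route to it is stated for a patient who has left treatment.

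**2. Can the size be derived from the plan?** No. The 10% in the sample size section is drop-out from the study, not from treatment, and is not split by arm. The sample size (88 per arm, 176 in total) is for the primary outcome. What follows is illustration on assumed figures.

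**3. Formula.** Assume no true effect, so both arms have overall mean μ. Let a proportion p leave treatment, let leavers score δ SD higher (worse) than stayers, and let only stayers be observed. Then:

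- stayers' mean in an arm = μ − p × δ
- intervention minus control among stayers = (μ − pI × δ) − (μ − pC × δ) = (pC − pI) × δ

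Higher SQ-48 means more distress, so a positive value counts against the intervention.

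**4. Numbers (all rates and δ assumed).**

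| Drop-out, control v intervention | δ = 0.3 | δ = 0.5 | δ = 1.0 |
|---|---|---|---|
| 10% v 10% | 0 | 0 | 0 |
| 15% v 10% | 0.05 × 0.3 = 0.015 | 0.05 × 0.5 = 0.025 | 0.05 × 1.0 = 0.05 |
| 20% v 10% | 0.10 × 0.3 = 0.03 | 0.10 × 0.5 = 0.05 | 0.10 × 1.0 = 0.10 |

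The range for unequal rates is 0.015 to 0.10 SD. With δ negative (leavers do better), the sign reverses.

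**5. Patients involved.** At 20% v 10%, 0.20 × 88 + 0.10 × 88 = 17.6 + 8.8 = 26.4, or about 26 of 176. This is a ceiling for those rates, because it assumes that every leaver lacks the T2 score.

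**6. Effect of the planned model.** The figures in step 4 are for crude means. The part of δ that T0 scores (and T1 scores, where present) predict is removed by a multilevel model that uses them. The remainder is not.

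**The case against.** A reader might infer that patients who leave care have no T1 or T2 score and that the SQ-48 is seen only in stayers. The documents do not support that. No section says that measurement ends when treatment ends. The word *only* in the quoted sentence limits which outcomes come through treatment; it does not say the SQ-48 can come from nowhere else. Table 2 gives it an X, like the research questionnaires, and not the patient-record mark used for drop-out and no-show. The general description of ROM also includes the end of treatment, although a score taken then would not be dated at T2. T1 is only two weeks after intake, so a patient who leaves later could still have T1 and lack only T2.

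A reader might also infer that ROM completion at T1 and T2 differs by arm because ROM is part of the intervention. The only stated difference is one extra ROM before the first consultation. No different T1 or T2 procedure is given, and ROM completion will be monitored and described.

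The protocol also plans intention-to-treat and a multilevel model, and a missing-data sensitivity analysis may sit in an analysis plan not shown here. Routine data are a defensible, low-burden choice.

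All of this narrows the point but does not remove it. The text and the table still need reconciling, and how a score is collected is not something a later analysis plan can repair.

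**Conclusion.** The protocol assigns the SQ-48 to treatment, schedules it for everyone at T1 and T2, and states no route for patients who stop. Because treatment drop-out is an outcome expected to improve with the new intake, SQ-48 availability may depend on retention and differ by arm. That is a risk of bias, mainly at T2, and not a demonstrated one.

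Its size and direction are unknown. The illustrative 0.015 to 0.10 SD rests on three assumptions: unequal drop-out of 15 to 20% against 10%, leavers 0.3 to 1.0 SD worse, and no adjustment for observed scores. One secondary outcome is concerned. The primary Decisional Conflict Scale is collected independently of treatment and is not affected, nor is the sample size. This is a cheap improvement, worth making because lost scores cannot be fully recovered in analysis.

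**What to change.** State in Study flow that research assistants request the SQ-48 at T1 and T2 from every consenting patient, regardless of treatment status, with the same e-mail, telephone and paper follow-up as the other forms. Allow a routine ROM completed within a stated window around T1 or T2 to stand in for it. Amend Randomisation and blinding and the Discussion so that they agree with Table 2: clinical outcome should no longer be listed as collected through treatment, and the SQ-48 should join the separately collected questionnaires.

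The cost is up to 48 extra items at T1 and T2 for patients without a recent ROM, and a small change to the patient information. The follow-up system already exists.
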